### Patient involvement

Patient involvement has been embedded in all phases of this study. The study design was developed in co-creation with a patient representative to ensure relevance and patient-centeredness. In addition, a UTI patient panel has provided structured feedback on patient information materials, perceived burden of study procedures, and potential barriers to participation. During the trial, enrolled participants will be invited to share their experiences through short surveys and focus groups to improve recruitment and patient-facing materials.

### Stakeholder and co-creation involvement

In addition to patient involvement, the study design was developed through a structured co-creation process involving a broad range of stakeholders. Representatives from national healthcare insurers, Knowledge Institute of the Dutch Association of Medical Specialists, the National Health Care Institute, and the professional associations for nursing, microbiology, infectious diseases, and urology participated in the co-creation phase. These stakeholders contributed to the selection of clinically meaningful outcomes, the operational feasibility of study procedures, the relevance and acceptability of the non-inferiority margin, and the anticipated implications for clinical practice and healthcare systems. Their input ensured that the study design reflects both clinical and societal perspectives and aligns with current implementation needs.

### Observational cohort

In addition to the RCT, an observational cohort will be established for adult patients with CAUTI who either decline participation in the intervention study or are ineligible based on the inclusion and exclusion criteria. These patients will be informed about the observational cohort and will be included only after providing written (or remote) informed consent. Baseline data and outcome measures will be extracted from the electronic medical record, and participants will be contacted once at 90 days by a member of the central study team at the LUMC to assess outcomes. Questionnaires and symptom diaries will not be collected in the observational cohort.

The observational cohort is included to enhance external validity and to provide insight into the characteristics and outcomes of patients who are not represented in the randomized trial. This allows assessment of potential selection and non-participation bias and enables comparison of baseline characteristics and clinical outcomes between trial participants and non-participants. In addition, the observational cohort will provide descriptive data on CAUTI management and outcomes in routine clinical practice, thereby facilitating interpretation and contextualization of the RCT findings.

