### Study interventions

Patients will be assessed for CAUTI according to standard practice of care. Potential participants will be screened against inclusion/exclusion criteria by the central study team. Eligible patients will receive written study information and provide written or remote informed consent before randomization.

After obtaining informed consent, participants will be randomized to either catheter replacement (control group) or catheter retention (intervention group). In the replacement group, the catheter will be replaced within 3 days of starting antibiotic treatment. All patients (men and women) will receive a 10-day course of antibiotics. The choice of antibiotic agent is at the discretion of the treating physician, except for nitrofurantoin, fosfomycin, and trimethoprim as these may be considered inferior for the treatment of CAUTI with systemic symptoms. Once culture and susceptibility results are available, therapy must be adjusted according to the EUCAST susceptibility criteria.

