### Data collection

Patients will be followed for a total period of 180 days, with seven telephone visits (Table 1). All follow-ups are done by a member of the central study team at the LUMC. Data will be collected on patient characteristics, symptoms, and urine analyses, and several questionnaires will be administered.

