#### Clinical data

At baseline, the following patient characteristics will be recorded: gender, age, height, weight, vital signs, social circumstances, medical history, medication use, catheter specific data (type of catheter, duration). The length of hospital stay, intensive care unit (ICU) admission during hospitalization, and type and treatment duration of antimicrobial agent(s) will additionally be collected.

Upon inclusion, CAUTI symptoms will be recorded, including onset or worsening of fever (> 38 degrees), rigors, altered mental status, malaise or lethargy with no other identified cause, flank pain, costovertebral angle tenderness, acute haematuria, pelvic discomfort, or suprapubic pain/tenderness. In patients with spinal cord injury increased spasticity, autonomic dysreflexia, or sense of unease will be assessed. Participants will be provided with a paper diary to record their symptoms for the first 14 days after start of antibiotic treatment. During each follow-up visit, CAUTI symptoms will be reassessed to track symptom duration and identify possible CAUTI recurrences.

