#### Questionnaires

Questionnaires will be administered at intermittent timepoints (Table 1). The PROMIS and EQ-5D-5 L will be used to assess health-related quality of life [15, 16]. Healthcare and societal costs will be evaluated using a selection of items relevant for this population of the medical consumption (iMCQ) and productivity (iPCQ) questionnaire [17]. If patients are able to complete questionnaires digitally, questionnaires are sent to the patient via Castor EDC.

**Table 1 Tab1:** An overview of the study visits and questionnaires administered during each visit

	Day 1	Day 3	Day 8	Day 15	Day 29	Day 60	Day 90	Day 180
CAUTI symptoms								
PROMIS								
EQ-5D-5 L								
iMCQ								
iPCQ								

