### Outcome measures

The primary outcome is a recurrent CAUTI within 90 days after completion of antibiotic treatment, defined according to the same IDSA-based clinical and microbiological criteria used for inclusion. The pathogen does not have to be identical to the causative pathogen that was identified during the first episode.

All participants are instructed to contact the central study team should they experience CAUTI symptoms. Additionally, the physicians at the participating centres and general practitioners are instructed to report potential recurrences among participants.

Secondary outcomes:

Patient-related outcomes: 30-day mortality, health-related quality of life assessed using the PROMIS and EQ-5D-5L questionnaires.Process-related outcomes: time to resolution of CAUTI symptoms, time to resolution of fever, complications of catheter replacement and severity of the complications (5-level Likert scale).Resource-related outcomes: length of hospital stay, ICU-admission during hospital stay, healthcare and societal cost using a selection of items relevant for this population of the medical consumption (iMCQ) and productivity (iPCQ) questionnaire.

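### Recurrence is sought more intensively in the trial than in the observational cohort, so comparing recurrence between participants and non-participants confounds ascertainment with selection

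*Protocol article*

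**What the plan says.** **Cohort.** The Observational cohort section of the protocol article takes outcomes from the electronic medical record and adds a single contact: "participants will be contacted once at 90 days by a member of the central study team". No questionnaires or diaries are collected. The section states that the cohort permits assessment of selection and non-participation bias, and that it "enables comparison of baseline characteristics and clinical outcomes between trial participants and non-participants". It adds no caveat about how outcomes are found in the two groups.

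**Trial.** The Data collection section gives randomised patients seven telephone visits over 180 days, at the times in Table 1 ("Day 1 Day 3 Day 8 Day 15 Day 29 Day 60 Day 90 Day 180", with Day 1 as baseline). Under Clinical data, the purpose of the calls includes finding recurrences: "During each follow-up visit, CAUTI symptoms will be reassessed to track symptom duration and identify possible CAUTI recurrences". The Outcome measures section adds reporting between calls: "All participants are instructed to contact the central study team should they experience CAUTI symptoms". Physicians at the centres and general practitioners are also told to report possible recurrences. The Observational cohort section mentions neither reporting route.

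**The concern.** Recurrent CAUTI is the trial's primary outcome and the obvious clinical outcome to compare with non-participants. It depends on symptoms being noticed and on a urine culture being taken. A patient who is asked repeatedly about symptoms, and told to call when they occur, is more likely to be recorded as having a recurrence than one asked once at 90 days. A late call also cannot supply a culture for an earlier episode that was never sampled.

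The external-validity statement is at stake. Lower recurrence in the cohort could mean that non-participants are at lower risk, or only that fewer of their episodes were found. Similar rates could hide a higher true risk among non-participants.

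**Working it through.** **1. The plan's own visit count.** Table 1 has eight columns. Less Day 1, that is 8 − 1 = 7 visits, which agrees with the stated seven. Six of them fall by Day 90.

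**2. Calls that matter for recurrence.** Outcome measures counts recurrence for 90 days after antibiotics are completed, and Study interventions fixes the course: "All patients (men and women) will receive a 10-day course of antibiotics". Taking Day 1 as roughly the start of antibiotics (an assumption), the course ends about Day 10 and the window closes about Day 10 + 90 = Day 100. The exclusion criteria allow a start up to 3 days before inclusion, which moves these dates by at most 3 days.

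- Days 3 and 8: before or at the edge of the at-risk period.
- Days 15, 29, 60 and 90: inside it.
- Day 180: well after it.

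The relevant contrast is four scheduled contacts against one.

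**3. The diary.** The trial diary is limited in time: "Participants will be provided with a paper diary to record their symptoms for the first 14 days after start of antibiotic treatment". It overlaps the at-risk period by about 14 − 10 = 4 days, so it adds almost nothing to the detection of recurrence.

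**4. Time origin.** The cohort section does not say from when its 90 days run. If they run from the start of antibiotics, the contact falls about 100 − 90 = 10 days before the window closes. The trial still has a Day 180 visit at which late episodes can be learnt of.

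**5. Side by side.**

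| Route to a recurrence | Trial | Cohort |
|---|---|---|
| Scheduled calls in the at-risk period | Days 15, 29, 60, 90 | One contact at 90 days |
| Patient told to call the team | Yes | Not stated |
| Physicians and general practitioners told to report | Yes | Not stated |
| Medical record | Stated for laboratory results | Stated for baseline data and outcomes |
| Urine culture | Standard of care | Not stated |

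**6. Illustration of size.** Let r be the share of recurrences found in the cohort relative to the trial. The documents give no value, so r is assumed. Take the 10% risk from the Sample size section as the rate seen in the trial.

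Apparent cohort rate = true cohort rate × r.

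| r (assumed) | Apparent cohort rate if the true rate is 10% | Spurious difference | True cohort rate that would look like 10% (10% / r) |
|---|---|---|---|
| 0.9 | 9% | 1 point | 11.1% |
| 0.8 | 8% | 2 points | 12.5% |
| 0.7 | 7% | 3 points | 14.3% |
| 0.5 | 5% | 5 points | 20% |

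**7. Would it be visible?** Assume 300 patients in each group (the cohort size is not given). The 95% interval is d ± 1.96 × √[p₁(1 − p₁)/300 + p₂(1 − p₂)/300].

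- r = 0.5: 0.05 ± 1.96 × √(0.09/300 + 0.0475/300) = 0.05 ± 0.042, or 0.8 to 9.2 points.
- r = 0.7: 0.03 ± 1.96 × √(0.09/300 + 0.0651/300) = 0.03 ± 0.045, or −1.5 to 7.5 points.

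Only strong under-detection would give an interval that excludes zero. Milder under-detection would still shift the estimate.

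**The case against.** The case on the other side has real weight.

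- **Shared constraints.** A recurrence must meet clinical and microbiological criteria, urine is cultured by standard of care, and no call-triggered culture is described. An uncultured episode therefore cannot count in either group. Both groups also have a 90-day contact by the same central team. This narrows the gap. It does not close it, because earlier calls can prompt care and sampling while symptoms are present.
- **The reporting routes may extend to the cohort.** Outcome measures addresses them to participants, a word the cohort section also uses for its own members. The text leaves this open, so it cannot be said that the routes are trial-only.
- **Record coverage.** The article refers to the electronic medical record without limiting it to the hospital, so missed episodes outside hospital are possible but not established.
- **The comparison is secondary and partly descriptive.** The Statistical analysis section plans no trial-versus-cohort estimate, and the details may sit in a fuller document. That is fair. The point, however, concerns a claim the article makes about what these data can show, not an omitted detail.

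A reader might go further and infer that the comparison measures ascertainment rather than selection, that cohort recurrence is bound to look lower, or that the contrast is seven calls and a diary against one call. The documents do not support this. They give no detection rate to show that ascertainment dominates, only four of the calls bear on the at-risk period, and the diary is nearly irrelevant to recurrence.

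**Conclusion.** The concern holds for recurrence and other outcomes that depend on symptoms being asked about. As described, a trial-versus-cohort difference in recurrence cannot be attributed to selection, because follow-up intensity differs as well. Under-detection in the cohort is the likely direction. That is an inference from the schedules, not a documented fact. The spurious difference of 1 to 5 points rests entirely on assumed relative detection of 90% to 50% and a 10% true risk in both groups. At parity of detection it would be zero.

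The reach is limited. The comparison of baseline characteristics, and the use of the cohort to monitor who declines (Strengths and limitations), do not depend on call frequency. Mortality, ICU admission and length of stay depend on it little. The randomised primary analysis, its margin and its power are untouched. This is a correction to the external-validity component, worth making because it is inexpensive and because the detection route may not be recoverable later.

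**What to change.** For the trial-versus-cohort comparison only:

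1. Define recurrence as culture-confirmed, record-documented CAUTI, extracted by the same rule, over the same window and from the same time origin in both groups. Supplement it in both groups only by the shared 90-day contact. Report it together with mortality.
2. Record prospectively how each trial recurrence was first detected: routine care, an extra scheduled call, patient or clinician report, or the 90-day contact. State whether the reporting routes apply to the cohort.
3. Run a sensitivity analysis that excludes episodes first detected through the extra trial calls. Keeping them leaves call-prompted care in the trial rate. Dropping them may over-correct, since some would have reached care anyway. The two versions together bracket the effect of those calls.
4. State in the Observational cohort section that the full trial recurrence rate is not directly comparable with the cohort rate.

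The primary outcome and its analysis stay as planned.

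**Cost.** One extra data field, a short protocol text and some additional record extraction for trial patients, since the article describes record use in the trial only for routine laboratory results. The comparison will rest on fewer events. Some bias will remain, because visits and cultures prompted by trial calls also enter the record.

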## Discussion

The REPLACE study outlined in this protocol is the first RCT with sufficient power to investigate the effect of catheter replacement in CAUTI. Even though CAUTIs are the most common healthcare-associated infection, current recommendations for catheter management during treatment are based on limited and conflicting evidence [8]. As a result of this evidence gap, considerable practice variation exists, underlining the need for this RCT to inform the guidelines and standardize practice.

### Strengths and limitations

One of the primary strengths of this study is its randomized, multicentre design, which enhances internal validity and generalizability. The planned sample size provides sufficient power to evaluate non-inferiority regarding recurrent CAUTI. In addition to traditional clinical outcomes, this trial includes patient-reported outcome measures, and a full economic evaluation, thereby capturing the impact of catheter management strategies on patients and healthcare systems alike. Another important strength is the extensive co-creation process. Patients, alongside experts from all relevant scientific associations (urology, infectious diseases and medical microbiology) were actively involved in shaping the study design. Their input was crucial in selecting relevant outcomes, the acceptability and feasibility of study procedures, and defining the clinically relevant non-inferiority margin. This collaborative approach increases the methodological robustness and the clinical relevance of the trial, and facilitates the implementation phase of the results. Additionally, the consistent antimicrobial therapy between both groups is a strength. Furthermore, the study adheres to the IDSA guideline definition of CAUTI, which incorporates both symptoms and urine culture results. This definition is consistently applied throughout the study, in both the inclusion criteria and recurrences, ensuring diagnostic consistency.

However, several limitations should be acknowledged. First, the inability to blind participants and clinicians may introduce reporting bias in symptom resolution and the reporting of recurrences. The risk of differential reporting is mitigated by the use of predefined symptom definitions, structured questionnaires, and centralised follow-up by a study team independent of clinical decision-making. A second challenge will be recruitment, as both patients and clinicians may have pre-existing preferences regarding catheter management and may not be willing to be randomized. To ensure adequate recruitment, additional study sites may be added if required. The observational cohort will allow us to monitor characteristics of patients who decline participation, thereby maintaining insight into potential non-participation bias.

Another limitation is the exclusion of potential participants who lack decision-making capacity (such as patients with delirium, dementia, or an intellectual disability), as the current inclusion criteria state that all participants must be able to provide informed consent. A substantial proportion of patients presenting with a CAUTI experience delirium or have pre-existing impaired decision-making capacity. Excluding these patients may therefore introduce selection bias and limit the generalisability of the study findings. An amendment in order to facilitate the participation of these patients is in preparation.

A further limitation is the potential for misclassification bias, which is well recognized in CAUTI research. Despite the use of the IDSA definition combining clinical and microbiological criteria, CAUTI remains a diagnostically challenging entity, and some degree of misclassification cannot be entirely excluded.

Lastly, the study population is limited to adults with a transurethral or suprapubic catheter. Patients with nephrostomy tubes or double-J stents are excluded, even though replacement is particularly burdensome in these populations and evidence is virtually absent. The findings of the REPLACE study cannot be directly extrapolated to kidney catheters, but they may provide a rationale for future studies investigating whether the conclusions of this trial hold true in these settings.

### Implications and future directions

Current national and international guidelines, advice to change the catheter with a low level of evidence [1, 7, 8]. If this trial demonstrate that catheter retention is non-inferior to replacement, clinical practice could be standardized accordingly in future guideline updates. This may reduce the number of invasive procedures, decrease healthcare costs, lower material waste and alleviate patient burden without compromising safety. Conversely, if catheter retention is not found to be non-inferior, the results will strengthen the evidence base supporting current recommendations for catheter replacement and may improve adherence in clinical practice.

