## Abstract

**Background:**

Catheter-associated urinary tract infection (CAUTI) is the most common healthcare associated infection. Current guidelines state that catheters should be replaced in patients with CAUTI to hasten symptom resolution and to lower the risk of recurrence. However, the available literature is limited and there is significant practice variation globally. The aim of this study is to determine whether not changing the catheter during CAUTI treatment affects the recurrence-risk.

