**Discussion:**

This trial will address a critical evidence gap and may inform future guidelines regarding catheter management in CAUTI. If replacement is found to have no benefit, this could reduce unnecessary interventions, lower healthcare costs and material use, contribute to sustainability, and lessen the burden on both patients and healthcare organizations.

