## Background

Due to the widespread use of urinary catheters, catheter-associated urinary tract infection (CAUTI) is the most common healthcare-associated infection [1]. As urinary catheter use is expected to rise with an aging population, the number of CAUTIs will likely increase accordingly [2]. CAUTIs can result in serious, sometimes fatal complications, including urosepsis [3–6].

To fasten recovery and reduce the risk of recurrent CAUTI, current guidelines recommend to replace the catheter at the onset of CAUTI when the indwelling catheter has been in place for more than two weeks [1, 6, 7]. This recommendation, however, is based on limited evidence as only four conflicting studies have been identified that investigate catheter replacement during CAUTI [8]. Current guidelines rely on only one of these four studies which is a small randomized controlled trial (RCT) that favoured catheter replacement [9]. The study reported shorter recovery times and lower recurrence rates in the replacement group compared to the retention group. These findings were contradicted by a second RCT [10], which found higher recurrence rates in the replacement group. However, in that study, antimicrobial treatment was shorter in the replacement group. Two observational studies found no effect of catheter replacement on either recurrence or symptom duration [11, 12], highlighting the paucity of the current state of evidence on catheter management during CAUTI.

In light of the limited evidence, a survey has been conducted to assess clinical practice regarding catheter management in CAUTI (manuscript in preparation [13]). It revealed considerable variation in catheter management practices among urologists, microbiologists, and internists. Urologists indicated more often that they routinely retain the transurethral catheter, compared to internists and medical microbiologists. The primary reasons for catheter replacement were the fact that it is a guideline recommendation and the expectation that replacement would be beneficial from a pathophysiological rationale. From a theoretical perspective, catheter replacement aligns with the principle of source control, as removal of the catheter may eliminate biofilm-associated pathogens that can persist during antimicrobial therapy and contribute to recurrent CAUTI [14]. Main reasons for retaining the catheter were the lack of scientific evidence supporting clinical benefit and the risk of procedural complications of the procedure.

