The REPLACE study aims to generate evidence to inform future recommendations for urinary catheter management in the treatment of CAUTI. We hypothesize that not changing the catheter during a CAUTI is non-inferior to replacing it with regard to the risk of recurrent CAUTI. This study therefore potentially contributes to reducing healthcare costs and sustainability by minimizing waste generated from catheter replacements, while also alleviating the workload on personnel when the procedure is redundant.

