#### Analyses of outcome measures

Descriptive statistics will be used to summarize baseline characteristics. In the primary analysis, the risk difference with (two-sided) 95% confidence interval will be computed to compare the differences in 90-day recurrence risk between the two treatment arms, in both the intention-to-treat population and the per-protocol population. Regarding the primary analysis, multiple imputation will be used to deal with missing outcome data (i.e. missing information regarding CAUTI recurrence). For the primary outcome, three sensitivity analyses will be performed to account for missing data. In the first sensitivity analysis, a complete case analysis will be performed. Additionally, a worst-case and best-case scenario analysis will be performed, in which patients who drop out of the study before 90 days will be included under the assumption that they experienced a recurrence (worst-case scenario) or no recurrence (best-case scenario), respectively.

The primary analysis will not take patient characteristics into account, as these are expected to be balanced between treatment groups (by randomization). In a secondary analysis, multivariable analysis will be performed including variables that are associated with recurrence of CAUTI.

The secondary outcome time-to-resolution will be analysed using Kaplan Meier survival analysis. For patient-related outcomes measures, such as PROMIS and EQ-5D-5 L, repeated measures analyses will be performed to compare these outcomes between the groups. For these outcome measures, multiple imputation will be used to deal with missing outcome data. Process and resource related outcome measures will be analysed in the per-protocol population. In addition, a cost-effectiveness analysis from a societal perspective with a 6-month time horizon and a budget impact analysis will be performed.

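### Non-inferiority is tested on recurrence only, but the stated practice implication carries no limit on slower symptom recovery, the other benefit that guidelines claim for replacement

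*Protocol article*

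**What the plan says.** The Abstract (Background) gives two reasons for current advice: "Current guidelines state that catheters should be replaced in patients with CAUTI to hasten symptom resolution and to lower the risk of recurrence". The main Background repeats both: "To fasten recovery and reduce the risk of recurrent CAUTI, current guidelines recommend to replace the catheter at the onset of CAUTI". Of the one small randomised trial on which guidelines rely, it says: "The study reported shorter recovery times and lower recurrence rates in the replacement group compared to the retention group".

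The trial's own hypothesis is narrower, namely that "not changing the catheter during a CAUTI is non-inferior to replacing it with regard to the risk of recurrent CAUTI". The 10% margin and the power statement under Sample size also concern recurrence only.

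Time to resolution of symptoms and of fever are listed under Outcome measures as process-related secondary outcomes. The analysis section says: "The secondary outcome time-to-resolution will be analysed using Kaplan Meier survival analysis". It assigns process-related outcomes to the per-protocol population.

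On what follows from the result, Implications and future directions says: "If this trial demonstrate that catheter retention is non-inferior to replacement, clinical practice could be standardized accordingly in future guideline updates". It adds that safety would not suffer, and that failure to show non-inferiority would strengthen the case for replacement. Neither branch mentions recovery. The Abstract (Discussion) uses a wider condition: "If replacement is found to have no benefit, this could reduce unnecessary interventions".

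**The concern.** The practice implication is wider than the tested hypothesis. Replacement is credited with two benefits and the trial tests the loss of one. Non-inferiority on recurrence says nothing about whether symptoms last longer when the catheter stays in, and it cannot establish that replacement has no benefit.

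The planned recovery analysis does not close the gap. As written it yields curves, with no stated size of delay that they could rule out. A non-significant difference between them may be taken as evidence of equal recovery, which it is not.

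The per-protocol restriction adds a risk. If patients in the retention arm who recover slowly have the catheter changed and then count as deviations, they leave the comparison and a delay is partly hidden. The article does not define the per-protocol set, so this is a possibility and not a finding.

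At stake is whether readers can tell what price in symptom duration, if any, is compatible with a positive result.

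**Working it through.** **Step 1: the plan's own figure.** Inputs from Sample size: 10% recurrence in both arms, margin 10 points, one-sided alpha 2.5%, 150 per arm.

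- SE = √(2 × 0.10 × 0.90 / 150) = 0.0346.
- Power = Φ(0.10 / 0.0346 − 1.96) = Φ(0.93) = 82.3%.
- Exact enumeration gives 81.9% with a Wald interval and 80.3% with a Newcombe interval or a score test.

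The stated figure of approximately 80% is reproduced. It applies to recurrence and to nothing else.

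**Step 2: what the recovery comparison can detect.** The documents give no mean, median or SD of symptom duration, so these are assumptions:

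- exponential durations with mean *m* = 3, 4 or 5 days under replacement;
- durations 25% longer under retention;
- 150 per arm, followed to day 14 (the length of the symptom diary) with no dropout;
- two-sided 5% log-rank test.

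Formulas:

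- Restricted mean to day 14 = *m*(1 − e^(−14/*m*)).
- Expected resolutions *D* = the sum over arms of 150(1 − e^(−14/mean)).
- Log-rank power ≈ Φ(ln 1.25 × √*D* / 2 − 1.96).

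Worked for *m* = 4, so a mean of 5 under retention:

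- Restricted means are 4(1 − e^(−3.5)) = 3.88 and 5(1 − e^(−2.8)) = 4.70, a difference of 0.82 day.
- *D* = 145.5 + 140.9 = 286.
- Power = Φ(0.223 × 16.9 / 2 − 1.96) = Φ(−0.07) = 47%.

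| Mean under replacement | Difference to day 14 | Power, formula | Power, simulation (2,000 trials) |
|---|---|---|---|
| 3 days | 0.69 day | 48% | 48% |
| 4 days | 0.82 day | 47% | 48% |
| 5 days | 0.89 day | 46% | 44% |

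In the simulation, power is 22 to 23% for a 15% lengthening and 79 to 82% for a 40% lengthening.

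**Step 3: a check without the exponential model.** For a difference in means, the largest non-significant value is 1.96 × SD × √(2/150). This is 0.45, 0.68, 0.91 and 1.13 days for SDs of 2, 3, 4 and 5 days. The order of magnitude agrees, and the spread shows how far it depends on the assumed SD.

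**Step 4: precision of an interval estimate.** Under the Step 2 model, the variance of time restricted to day 14 is 2*m*²[1 − e^(−14/*m*)(1 + 14/*m*)] minus the squared restricted mean. The SDs are 2.87, 3.55 and 4.05 days for means of 3, 4 and 5.

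- With no true delay, the 95% half-width is 1.96 × SD × √(2/150) = 0.65, 0.80 and 0.92 day.
- With a 25% lengthening, the SEs are 0.36, 0.44 and 0.49, so the half-widths are 0.71, 0.86 and 0.96 day.

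The half-width is thus about 0.65 to 1.0 day, which is informative enough to report.

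**Step 5: could a bound on delay act as a gate?** Take an illustrative bound of 1 day and no true delay. The chance that the upper limit lies below it is Φ(1/SE − 1.96), with SE = 0.33, 0.41 and 0.47. This gives 86%, 68% and 57%. Multiplied by 82% for recurrence (treating the two results as independent), the chance of meeting both is about 70%, 56% and 47%.

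**The case against.** The strongest reply is that the quoted sentence is not a decision rule. It is conditional, it looks ahead to future guideline updates, and it leaves the decision to people who will see every outcome. Elsewhere the tested claim is scoped correctly: the hypothesis and the power claim under Strengths and limitations name recurrence. Recovery is well covered by a 14-day diary, reassessment at each visit, and quality-of-life measures. One margined primary outcome with unmargined secondaries is ordinary design, and detail on secondary estimates may sit in an analysis plan that is not shown. The Background also reports two observational studies that found no effect of replacement on symptom duration.

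Much of this stands, and it rules out three stronger readings:

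- **That the plan would adopt retention on recurrence alone, whatever happens to recovery.** The text says only that practice could be standardised, and recovery will be analysed. The Abstract's no-benefit condition is not restricted to recurrence, so a demonstrated delay would defeat it.
- **That retention could slow recovery by most of a day unnoticed, as a fact about this trial.** That size comes entirely from assumed durations.
- **That the practice conclusion must be gated on a margin for delay.** Step 5 shows this would be a second criterion for which the trial is not powered. It would also rest on symptom reports that the article itself says are open to bias, because the trial is unblinded.

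The reply does not remove the mismatch. The implications paragraph drops the qualification to recurrence, adds a reassurance on safety, and draws its conclusions in both directions from one result. An unseen analysis plan could refine the recovery analysis but would not change that published interpretation.

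**Conclusion.** The concern holds as a mismatch between what is tested and what is concluded. It is neither an arithmetic error nor a missing outcome. Guidelines claim two benefits for replacement, non-inferiority is tested on one, and the practice implication places no limit on loss of the other.

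Under the stated assumptions (exponential durations, mean 3 to 5 days, 150 per arm, complete diaries), a 25% lengthening would be missed in 52 to 56% of trials. A non-significant curve comparison therefore could not be read as preserved recovery. Nothing in the documents says that it will be read that way; the point is that the plan fixes nothing to prevent it. The sizes would change with the true spread of symptom duration, but the logical gap would not.

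**What to change.** 1. **Analyses of outcome measures:** beside the Kaplan-Meier curves, report the between-arm difference in restricted mean time to symptom resolution up to day 14 with a two-sided 95% confidence interval. Do so by randomised arm (intention-to-treat) as well as per protocol.
2. **Abstract (Discussion) and Implications and future directions:** limit the non-inferiority conclusion to recurrence. Beside any statement about practice, give the recovery delay that the interval does not exclude.
3. **Optional:** the stakeholder group that advised on the recurrence margin could agree an acceptable delay before the data are seen. It should serve as an aid to interpretation and should not gate the conclusion, because the trial is not powered for it.

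The cost is one extra analysis of diary data already being collected and a few sentences of wording, with no extra patients or procedures. The downside is a somewhat narrower conclusion.
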